## Abstract

It is crucial for human health that the immune system of the gastrointestinal tract works effectively. Dietary modulation is one of the factors that regulate the immune response in the gut. This study aims to develop a safe human challenge model to study gastrointestinal inflammation and immune function. This study focuses on evaluating gut stimulation induced by the oral cholera vaccine in healthy people. In addition, this paper describes the study design for assessing the efficacy and safety of a probiotic lysate, identifying whether functional ingredients in food can modulate inflammatory response induced by oral cholera vaccine. Forty-six males aged 20 to 50 with healthy bowel habits will be randomly allocated to the placebo or intervention group. Participants will consume 1 capsule of probiotic lysate or placebo twice daily for 6 weeks, take oral cholera vaccines on visit 2 (day 15) and visit 5 (day 29). The level of fecal calprotectin, a marker of gut inflammation, will be the primary outcome. The changes of cholera toxin-specific antibody levels and local/systemic inflammatory responses will be evaluated in blood. The purpose of this study is to evaluate gut stimulation of the oral cholera vaccine and investigate the effect of a probiotic lysate on improving the mild inflammatory response induced by the vaccine or supporting the immune response in healthy subjects.

**Trial registration**: * This trial is registered in the International Clinical Trials Registry Platform of WHO (ICTRP, registration number: KCT0002589).

## Introduction

Normal functioning of the immune system is essential for physical health, and dietary compounds are believed to play a role in maintaining or strengthening immune function [1]. To demonstrate beneficial immune effects of food ingredients, food regulatory authorities in general request proof of reduced incidence, severity, or duration of infections. Additionally, some regulatory authorities allow the use of vaccination-induced immune responses to demonstrate the effect of beneficial physiological effects of food ingredients or supplements on the immune system [2].

In the general population, increased inflammation or immune responses due to challenge could provide more sensitive indications than measuring markers in steady-state, and vaccination could potentially be a standardized challenge applicable to nutritional intervention studies [3]. Dietary modulation of the response to oral vaccination could be a good model for studying the effect on gastrointestinal inflammation and gut permeability. The Attenuated enterotoxigenic *Escherichia coli* (ETEC) strain, developed initially as a potential vaccine, is already used in a challenge model. However, as it induces gastrointestinal symptoms, the primary readout in this model is the symptoms [4, 5]. To investigate gastrointestinal inflammation and immune response, a model with a lower burden for study participants is preferred.

The oral cholera vaccine (Dukoral^®^) consists of 1.25×10^11^ inactivated Vibrio cholera bacteria and 1 mg recombinant cholera toxin B-subunit (rCTB) per dose, provided with Sodium Hydrogen Carbonate. CTB is non-toxic and is a potent mucosal immunogen due to its affinity binding to the receptor GM1 ganglioside [6]. It could be used as a carrier for antigens and improve mucosal immunity [7]. It is hypothesized that the binding of the CTB induces an inflammatory reaction, however how strong or how extensive the inflammatory reaction is, has not been investigated yet.

*Lactobacillus plantarum* is listed in the Korean Health Functional Food code [8] and is a representative probiotic that appears in the fermenting season among the lactic acid bacteria in Kimchi, a Korean traditional fermented food. Lipoteichoic acid (LTA), a component acquired from the cell wall, was considered a proinflammatory molecule of Gram-positive bacteria [9]. However, in several studies, LTA separated from beneficial bacteria such as *Lb*. *plantarum* showed weak nitric oxide production compared to pathogen and attenuated the induced inflammation [9–12]. Also, our previous study showed that *Lb*. *plantarum* K8 lysate regulated Toll like receptor-2 signaling, prevented DSS-induced intestinal mucosal damage, and reduced increased proinflammatory cytokines in rats [13]. Therefore, we expect *Lb*. *plantarum* K8 lysate to help regulate the balance of the intestinal immune system. However, the efficacy of *Lb*. *plantarum* K8 lysate on gut immunity in the general population has rarely been studied.

In this study, we aimed to develop a new human intervention study protocol that can be used to study gastrointestinal inflammation. Because of the immunogenicity of the cholera vaccine targeting the gut, we aim to provide support for our concept that, in addition to inducing a protective immune response, this vaccine might also be used as a safe approach to induce a mild gastrointestinal inflammatory response in healthy human subjects, as a challenge model for dietary intervention studies. To study whether this inflammatory response or the vaccination response can be modulated by an active ingredient, we use *Lb*. *plantarum* K8 lysate as an intervention.

## Methods

### Ethics approval

The Institutional Review Board (IRB) of Ewha Womans University Medical Center approved the study (EUMC 2017-05-068) on 05/07/17. This trial is registered in the International Clinical Trials Registry Platform of WHO (ICTRP, registration number: KCT0002589) and available at https://cris.nih.go.kr. This study will be performed according to Good Clinical Practice and the Declaration of Helsinki. Informed consent will be documented with a written consent form approved by the IRB and signed by the participant or the participant’s legally authorized representative. A copy will be given to the person who signed the form.

### Study design

This study is a randomized, double-blind, placebo-controlled, parallel-group study investigating the efficacy and safety of probiotics lysate in modulating local and systemic inflammation. Participants will be screened according to inclusion/exclusion criteria, including a brief medical examination after voluntarily signing the informed consent form. Eligible subjects will be randomly allocated to either treatment or placebo groups. The schedule of enrollments, interventions, and assessments is shown in the SPIRIT flow diagram (Fig 1).

**Fig 1 pone.0281817.g001:**
[figure not shown]
SPIRIT flow diagram. Flowchart of schedule of enrollments, interventions, and assessments. IgA = immunoglobulin A, IgG = immunoglobulin G, I-FABP = Intestinal fatty-acid binding protein, IP10 = Interferon gamma-induced protein 10, hsCRP = high-sensitivity C-reactive protein, IL-1ra = interleukin-1 receptor antagonist, AST = aspartate aminotransferase, ALT = alanine aminotransferase.

### Sample size calculation

The sample size for the placebo group and the treatment group will be registered for a total of 46 people, 23 per group, in consideration of the 20% drop-out rate. The required sample size was calculated for the calprotectin level in feces and C-reactive protein (CRP) in plasma. According to the results of previous research, we assumed that the calprotectin level (mean ± SD) in healthy individuals is 15 ± 20 μg/g feces [4]. In healthy adults, an increase to 50 μg/g is considered an upper limit [14]. Based on two-sided statistical testing for paired data, α = 0.05 (chance on a type-I error) and β = 0.10 (chance on a type-II error), 19 subjects per group are needed for this outcome. For C-reactive protein, it was shown that the plasma level in low-grade inflammation is 2.54 ± 2.07 mg/L (mean ± SD), as compared to 1.01 ± 0.88 mg/L in normal individuals [15]. Assuming that cholera vaccination will increase CRP to a similar extent compared to baseline in the placebo group, based on two-sided statistical testing for paired data, α = 0.05 (chance on a type-I error) and β = 0.20 (chance on a type-II error), 18 subjects are calculated per group for this outcome.

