### Participants and eligibility criteria

Participants will include males between 20 and 50 years old. Considering the dropout rate of 20%, 46 eligible participants will be recruited from Ewha Womans University Medical Center. The inclusion/exclusion criteria are as follows.

Inclusion Criteria:

A subject who voluntarily agrees to participate and sign the informed consent formMale (aged 20 to 50 years)Healthy bowel habits (A person who defecates regularly at least four times a week and once a day (less than two times))Availability of internet connectionSmartphone user

Exclusion criteria:

Previous cholera vaccination historyOther vaccination in the past 1 monthAcute gastroenteritis in the past 2 monthsUse of antibiotics in the past 2 monthsHypersensitivity to the vaccine, to formaldehyde, to any of the excipients (sodium salts), or to probioticsThe disease of GI tract (constipation, diarrhea, Inflammatory bowel disease, etc), liver, gall bladder, kidneys, thyroid glandImmune-compromisedUse of immunosuppressive drugsDrug abuse, and not willing/able to stop this during the studyContinuous consumption of probiotics within 2 weeks prior to the studyExcessive alcohol usage (140 g/week, about 3.5 bottles/week or 4 glasses/day as soju)Participating in another clinical trial within 12 weeks prior to or during the studyVisiting a country affected by cholera in the past 1 month

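### At the stated 20% drop-out, 23 per group leaves 18.4 expected completers, just short of the 19 required for calprotectin

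*Protocol article*

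**What the plan says.** The protocol article names one primary outcome in its Abstract: "The level of fecal calprotectin, a marker of gut inflammation, will be the primary outcome". The Sample size calculation section then gives two requirements, both for two-sided paired testing at α = 0.05:

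- Calprotectin, with 90% power: "19 subjects per group are needed for this outcome".
- CRP, with 80% power: "18 subjects are calculated per group for this outcome".

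The same section opens with the enrolment figure: the two groups "will be registered for a total of 46 people, 23 per group, in consideration of the 20% drop-out rate". The Participants and eligibility criteria section repeats it: "Considering the dropout rate of 20%, 46 eligible participants will be recruited".

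Neither section shows the step from 19 or 18 to 23.

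**The concern.** Calprotectin is the primary outcome and has the larger requirement, so 19 per group is the number that enrolment has to protect. A drop-out allowance of 20% should leave at least 19 per group once 20% are lost. With 23 enrolled it does not. The required number, the drop-out rate and the enrolment figure therefore cannot all hold. What is at stake is whether the sample-size statement for the primary outcome is accurate, and a small amount of power. The design itself is not in question.

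**Working it through.** **Inputs.** All come from the protocol article. Required per group: 19 (calprotectin, β = 0.10) and 18 (CRP, β = 0.20). Drop-out: d = 20%. Enrolment: 23 per group, 46 in total. Allocation: 1:1.

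**Reproducing 23.** The number to enrol so that n remain after a proportion d is lost is n/(1 − d). A common shortcut, n × (1 + d), gives too few.

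| Starting from | n/(1 − d) | n × (1 + d) |
|---|---|---|
| 19 (calprotectin) | 19/0.8 = 23.75 → 24 | 19 × 1.2 = 22.8 → 23 |
| 18 (CRP) | 18/0.8 = 22.5 → 23 | 18 × 1.2 = 21.6 → 22 |

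Two routes give the stated 23: the shortcut applied to 19, and correct division applied to 18. The article does not say which was used, if either. Correct division applied to the primary-outcome requirement gives 24.

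**Completers at 20% drop-out.**

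- Per group: 23 × 0.8 = 18.4. This is below 19 and above 18.
- In total: 46 × 0.8 = 36.8, against 2 × 19 = 38.
- In whole subjects: 9 lost of 46 (19.6%) leaves 37, so at least one group has fewer than 19.
- With 24 per group: 24 × 0.8 = 19.2, which meets 19.

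**Drop-out that 23 can absorb.** 23 − 19 = 4 and 4/23 = 17.4%.

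**Effect on power, if 19 gives exactly 90%.** By the normal approximation, the standardised paired difference that has 90% power at n = 19 is (1.960 + 1.282)/√19 = 0.744.

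- At n = 18: Φ(0.744 × √18 − 1.960) = 88.4%.
- At n = 18.4: 89.1%.
- The paired t-test version (standardised difference 0.787 for 90% at n = 19) gives 88.2% at n = 18.

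The loss is therefore about 1 to 2 percentage points.

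**The case against.** Four arguments can be made against the point.

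**Drop-outs may still contribute data.** The Statistical analysis section includes all data from subjects who received the product and adds a linear mixed-effects model, which can use partial records. Fecal samples are taken on days 14, 16 and 17, around the day-15 vaccination, so a subject who leaves after day 17 still supplies a pre/post pair for the first dose. That much stands: 18.4 counts completers and is not necessarily the number available for every paired contrast. It does not rescue the figure. The calculation is for paired data and adds its own drop-out allowance, so it treats drop-outs as lost. The per-protocol set, restricted to compliant completers, cannot be larger than the number of completers.

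**The 23 may come from CRP.** It may, and for CRP it is sufficient. A reader might infer from 19 × 1.2 that the wrong inflation formula was used. The article does not support that as a fact, because 18/0.8 fits equally well. On either route the 19 for the primary outcome is not protected.

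**The 90% is not necessarily missed.** The 88% holds only if 19 is exactly sufficient. The section's own calprotectin figures are 15 ± 20 μg/g and an upper limit of 50 μg/g. Read as a change of 35 with SD 20, they would need only (20 × 3.242/35)² = 3.4, so 4 subjects by the normal approximation (6 by the t-test), and power at 18 would be above 99.9%. This stands as a condition on the power figure. How 19 was obtained is a separate question; here it is taken as stated.

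**A planning assumption is only approximate.** The 20% is a guess, and 23 per group tolerates 17.4%. This is fair, and it is why the point is minor. The stated numbers still disagree as written.

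**Conclusion.** The sample-size statement is wrong as written, and the error is minor. At the stated 20% drop-out, 23 per group leaves 18.4 expected completers against the 19 required for calprotectin; 24 per group would be needed. The CRP requirement of 18 is met. The gap is 0.6 of an expected completer per group, or one enrolled participant per group. The power cost is about 2 points at 18 per group (about 88% instead of 90%), conditional on 19 giving exactly 90%. The conclusion takes the 19 and the 20% as stated and assumes, as the calculation does, that drop-outs are lost to the paired comparison.

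A reader might go further and infer that the trial is seriously at risk of missing its target. With independent 20% drop-out, the chance of at least 19 completers from 23 is 50% in one group and 25% in both. Those figures mostly reflect chance variation: with 24 per group they are still only 66% and 43%. They do not show that the trial is materially underpowered, and nothing here touches the validity of the design.

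**What to change.** Keep 46 and correct the statement in both places, Sample size calculation and Participants and eligibility criteria. Suggested content: 23 per group retains the required 19 for drop-out up to about 17% (4 of 23); at 20% drop-out about 18 per group remain, which meets the CRP requirement and falls slightly short of the calprotectin requirement (about 88% instead of 90% power, if 19 gives exactly 90%). The condition on the power figure should stay in the text, because the article does not show how 19 was derived.

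The cost is one reworded sentence in two sections and a slightly less favourable stated figure. Enrolment does not change. If the sponsor prefers to keep both the 20% and the 19, the consistent enrolment is 24 per group, 48 in total. That costs two more participants and also changes the total given in the Abstract.

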### Participants and eligibility criteria

Participants will include males between 20 and 50 years old. Considering the dropout rate of 20%, 46 eligible participants will be recruited from Ewha Womans University Medical Center. The inclusion/exclusion criteria are as follows.

Inclusion Criteria:

A subject who voluntarily agrees to participate and sign the informed consent formMale (aged 20 to 50 years)Healthy bowel habits (A person who defecates regularly at least four times a week and once a day (less than two times))Availability of internet connectionSmartphone user

Exclusion criteria:

Previous cholera vaccination historyOther vaccination in the past 1 monthAcute gastroenteritis in the past 2 monthsUse of antibiotics in the past 2 monthsHypersensitivity to the vaccine, to formaldehyde, to any of the excipients (sodium salts), or to probioticsThe disease of GI tract (constipation, diarrhea, Inflammatory bowel disease, etc), liver, gall bladder, kidneys, thyroid glandImmune-compromisedUse of immunosuppressive drugsDrug abuse, and not willing/able to stop this during the studyContinuous consumption of probiotics within 2 weeks prior to the studyExcessive alcohol usage (140 g/week, about 3.5 bottles/week or 4 glasses/day as soju)Participating in another clinical trial within 12 weeks prior to or during the studyVisiting a country affected by cholera in the past 1 month

### Recruitment

Subjects will recruit using posters and advertisements (online and/or offline) with a brief explanation about the research and the investigator’s contact information in Ewha Womans University Medical Center and the surrounding area. Those who want to participate in this study will obtain detailed information about the study from trained research coordinators.

### Randomization, allocation concealment, and binding

Participants will be randomly assigned (1:1) to a placebo or treatment group. Study products will be provided by Sempio Co., Ltd. (Seoul, Korea). This will be a double-blind trial, the product will be blinded to the subjects, investigators, and coordinators throughout the study period. The code list identifying the product consumed by each subject will be opened only at the end of the study, after data analysis, or earlier in case of medical necessity.

### Handling of withdrawal

Participants can withdraw from the study for any reason at any time. If the subject decides to withdraw the consent, the investigator will ask the reason for the withdrawal and document it in the case report form (CRF). The subject may be removed from the study for the following reason:

A subject requests discontinuation; the principal investigator (PI) initiates removal for medical or compliance reasonsOccurrence of an adverse event that is considered serious by the PIOccurrence of an illness that affects the subject’s further participationAny other reason considered by the PI to be necessary for a subject’s safetyNon-compliance with study procedures

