### Safety variables

Blood chemistry and vital signs will be monitored at every visit. Aspartate Aminotransferase (AST) and Alanine Aminotransferase (ALT) will be measured on days 0 and 43. Vital signs (body temperature, systolic/diastolic blood pressure, and pulse rate) will be confirmed at every visit. Unusual signs will be monitored by online questionnaires during the study. Unintended changes in pathological, anatomical, metabolic, or physiological functions associated with the use of a study product are considered side effects, except for changes associated with normal activities that are ordinarily clinically expected to change in frequency or magnitude form. The PI will assess all AEs as to their severity and relation to the study product. Appropriate treatment and follow-up will be performed, which will continue until the condition is resolved or the cause is identified.

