### Compliance

Compliance will be assessed biweekly by interviewing subjects and counting the study product returned to the clinic. Consuming less than 80% of the scheduled intakes will be defined as non-compliance. Subjects will be called as appropriate to encourage compliance.

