### Statistical analysis

Data analyses will be performed with intention-to-treat subject data (all data from subjects who have received the study product) or per-protocol subject data (only data from subjects who completed the study at least 80% compliant with the study product). Variables will be tested for normal distribution and data transformation will be performed on skewed variables. Parametric or non-parametric analyses (dependent on the outcome of the distribution of data) such as paired *t*-test, Student’s *t*-test, or Wilcoxon signed-rank test will be used to analyze the difference within each group or between the groups for continuous variables. Chi-square or Fisher’s exact test will be used to analyze the difference between the groups for categorical variables. A linear mixed-effects model with group and time as fixed effects and subject as the random effect will be applied to compare the changes between groups over the intervention period. The correlation between variables will be analyzed by Pearson’s correlation or Spearman correlation and regression analysis will be performed. The data will be analyzed using the SAS 9.4 statistical software. The difference between the groups will be tested two-sided for all study outcomes. *P*-values <0.05 are classified as statistically significant.

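### The withdrawal rule offers only removal from the study, so action on medical or compliance grounds can cut short the scheduled sampling that the intention-to-treat analysis needs

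*Protocol article*

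**What the plan says.** Handling of withdrawal first covers a participant who withdraws consent. It then turns to removal: "The subject may be removed from the study for the following reason". The grounds listed are:

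- the subject's own request;
- removal by the principal investigator on medical or compliance grounds;
- an adverse event that the investigator regards as serious;
- an illness that bears on further participation;
- any other safety reason;
- failure to comply with study procedures.

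No intermediate step is described in which the product or the second vaccine dose stops and sampling goes on.

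Three other sections bear on this:

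- Compliance: "Consuming less than 80% of the scheduled intakes will be defined as non-compliance". It is checked every two weeks.
- Statistical analysis: one analysis set is "intention-to-treat subject data (all data from subjects who have received the study product". The other, per-protocol, is "only data from subjects who completed the study at least 80% compliant with the study product". For change over time, "A linear mixed-effects model with group and time as fixed effects and subject as the random effect will be applied". Paired and two-sample tests are planned as well.
- Safety variables, on adverse events: "Appropriate treatment and follow-up will be performed, which will continue until the condition is resolved or the cause is identified".

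**The concern.** An intention-to-treat comparison needs outcomes from randomised men whether or not they stay on product. Here the only tool given to an investigator who wants to stop the product is an exit from the study, so the later outcomes are never collected.

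Two consequences follow. First, if men with low intake are removed, the intention-to-treat data after that point come increasingly from compliant men. That restriction is what the per-protocol set is for. Second, if men are removed for medical reasons arising after randomisation, the loss may be related to how they responded to the vaccine or to which arm they were in. At stake are the estimate of the vaccine response, the comparison of lysate with placebo, and the completeness of scheduled safety data in a trial that sets out to show a safe challenge model.

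**Working it through.** **1. The plan's own allowance for loss.** Sample size calculation enrols "a total of 46 people, 23 per group, in consideration of the 20% drop-out rate", from 19 needed per group for calprotectin.

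- 19 × (1 + 0.20) = 22.8, rounded up to 23, which reproduces the stated figure.
- Dividing by the retained fraction gives 19 / 0.80 = 23.75, rounded up to 24.
- At the planned loss, 23 × 0.80 = 18.4 men per group remain, just under 19. There is no reserve for avoidable loss.

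**2. What a removal costs, by timing.** Outcome measures schedules stools on days 0, 14, 16, 17, 28, 30, 31 and 42, with vaccine on days 15 and 29. Six of the eight follow the first dose.

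| Removed on | Stools lost | Number |
|---|---|---|
| Day 15, before dose 1 | 16, 17, 28, 30, 31, 42 | 6 |
| Between days 17 and 28 | 28, 30, 31, 42 | 4 |
| Day 29 | 30, 31, 42 | 3 |
| After day 31 | 42 | 1 |

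The article gives no calendar days for the biweekly compliance checks. Counting two-week steps from day 1 puts them near days 15, 29 and 43. A man removed at the first of these would stay in the intention-to-treat set with no post-vaccine stool at all.

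**3. Convergence of the two analysis sets.** Suppose every man below 80% intake is removed when this is found. After that point, the intention-to-treat data contain only men not yet found non-compliant. By day 42 they differ from the per-protocol data only through men whose low intake was not acted on. The article does not say that the 80% definition triggers removal. It does name compliance as a ground, so the investigator may use it in this way.

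**4. What the planned analyses do with truncated series.** A paired t-test or signed-rank test drops a man who lacks the later sample. The trial is also sized on such a test: "Based on two-sided statistical testing for paired data, α = 0.05 (chance on a type-I error) and β = 0.10 (chance on a type-II error". The mixed model keeps his earlier values and is valid if the loss is explained by observed data. An event between two scheduled stools need not be predicted by earlier calprotectin.

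**5. Scale, under stated assumptions only.** The paired normal formula is n = (SD × (1.960 + 1.282) / change)².

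- SD 20 and change 15: n = 18.7, so 19, the plan's figure. The article does not state a change of 15.
- SD 20 and change 35 (from 15 to 50): n = 3.4, so 4. The rise named in the text does not give 19.

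I therefore take a normal change with mean 15 and SD 20 as an assumption for 23 men in one group.

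- If loss is unrelated to response, the expected mean stays at 15. Paired t-test power is 0.93 with 23 men, 0.87 with 19, 0.85 with 18 and 0.80 with 16.
- If the men lost are exactly the one, two or three largest responders and contribute no change value, the simulated mean falls to about 13.3, 11.8 or 10.4.

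The second line is an extreme case. Nothing in the document says how many men would be removed or that they would be the largest responders.

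**The case against.** The strongest reply is that this is a condensed article, and that data collection after discontinuation is often left to the full protocol or analysis plan. That limits the point but does not remove it: the article states a rule, removal from the study, and the concern is with following that rule as printed.

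Several stronger readings are tempting, and the document does not support them.

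- **That the intention-to-treat set is emptied.** Everyone who received product stays in it with data up to removal, and a mixed model that can use partial series is planned.
- **That safety follow-up ends.** Safety variables continues follow-up of the adverse event. Only the scheduled assessments after removal are left uncovered.
- **That any reaction leads to removal.** Removal is discretionary. The adverse-event ground is limited to events the investigator regards as serious, and the illness ground to illness affecting participation.
- **That the strongest calprotectin responders are the men lost.** A raised calprotectin is not a ground for removal, and the expected response is mild. The link is an inference. Losing the day 16 and 17 stools would also need removal within a day or two of the first dose.
- **That the bias can be calculated around a target mean of 50 μg/g.** The article gives 50 as an upper limit in healthy adults, and its 20% drop-out allowance is not tied to these removals.

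It is also fair to say that the per-protocol set deals with completion and product intake. It does not deal with missed visits or samples, so it cannot by itself replace the ground on study procedures.

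**Conclusion.** The point holds in a limited form. The withdrawal rule does not separate stopping product or vaccine from stopping data collection, so following it truncates later outcome and scheduled safety data in men who remain in the intention-to-treat set. The compliance part needs no assumption about who reacts: removing men for low intake moves that analysis toward the per-protocol one. The medical part is a possibility only, since such removals may or may not be related to response or arm.

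The direction and size of any bias cannot be derived from the document. A reader might infer that the vaccine response will be understated and look safer than it is. That follows only if removals fall mainly on strong responders, which nothing in the article establishes. The avoidable loss of scheduled data is enough to justify a change this cheap.

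**What to change.** Reword Handling of withdrawal so that action by the investigator on medical or product-compliance grounds is discontinuation of the study product and/or vaccine. Whether and when to do so stays with the investigator and the sponsor. Then state that the stool, blood, stool-survey and safety assessments already scheduled continue to day 43, unless the subject withdraws consent or the investigator judges an assessment unsafe.

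State also that low product intake does not by itself end data collection, because the per-protocol set already handles it. Missed procedures should be recorded as missing data and should not trigger removal.

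The cost is protocol wording and some effort to retain men who are off product. No visit or assay is added beyond the existing schedule.
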